## Abstract

**Background:**

Asylum seekers and refugees are at great risk for developing mental disorders. Afghan refugees are a particularly vulnerable group with a low average education and mental health literacy level. Traumatic experiences and hardship before and during migration are predictive of mental health problems. However, post-migration living difficulties (PMLDs) also account for a large proportion of mental distress in such populations, which, critically, are not sufficiently considered in treatment protocols and research investigations. Indeed, the evidence base for the treatment of refugees and asylum seekers is sparse and limited mainly to trauma-specific treatments, where refugees may likely suffer from other mental health problems such as depression or anxiety.

**Methods/design:**

This trial is the first evaluation of a short-term, transdiagnostic treatment protocol for treatment-seeking Afghan refugees which addresses mental health problems and PMLDs while using an adapted version of the Problem Management Plus (PM+) protocol. Here, we will investigate the efficacy of an intervention manual with a prospective, single-center, randomized, assessor-blind, two-group trial among refugees who are on a waiting list for professional mental health treatment. Furthermore, we will investigate participants’ subjective experiences with the intervention manual via in-depth interviews. One hundred twenty people will be assessed and randomly allocated to either the intervention arm or a treatment-as-usual arm. Clinical psychologists will conduct the treatment, and the sessions will take place with a Dari interpreter. The protocol consists of six 90-min sessions. The primary endpoint is the general symptom distress measure, assessed with the General Health Questionnaire 28 (GHQ-28). Secondary endpoints are the Post-Migration Living Difficulties Checklist (PMLDC), the International Trauma Questionnaire (ITQ), the World Health Organization Quality of Life Questionnaire (WHOQOL-BREF), the Psychological Outcome Profile (PSYCHLOPS), service and health care use (assessed with several items), and the Immigrant Integration Index (IPL-12).

**Discussion:**

This trial may provide substantial evidence for a brief transdiagnostic psychological intervention. Here, we intend to contribute to the treatment of mental health problems among Afghan refugees. The assessment of subjective experience with this treatment manual, as well as the evaluation of its clinical applicability, may optimize treatment acceptance and outcomes across a wide range of mental health problems among refugees.

**Trial registration:**

German Clinical Trials Register (DRKS) registration number: DRKS00016538. Universal Trial Number: U1111-1226-3285. Registered on January 7, 2019. https://www.drks.de/drks_web/setLocale_EN.do

## Background

In the present study, we intend to contribute to the treatment of mental illness among Afghan asylum seekers and refugees. There are currently 2.5 million refugees from Afghanistan, making this group the second largest refugee population in the world [1]. In Austria, people from Afghanistan represented the largest group of asylum seekers from 2001 to 2016 and, since then, the second largest group after Syrian asylum seekers [2]. Indeed, once refugees have arrived in a safe country, many individuals suffer from various mental disorders [3] such as post-traumatic stress disorder (PTSD), depression, and anxiety disorders [4, 5]. Critically, individuals who experience traumatic events are also at greater risk to develop other mental disorders [6]. Of importance, the severity of mental illnesses may be even worse for asylum seekers who do not have an official refugee status [7], and it has been shown that the longer the asylum procedure takes, the higher the risk is for future mental health problems [5]. Research has consistently found that traumatic experiences and hardship, experienced both in the country of origin and during migration, are predictive of mental health problems. Interestingly, post-migration living difficulties (PMLDs) are also predictive of mental health problems [8–11], yet they are seldom addressed in psychological therapies or empirical research investigations [12]. The treatment evidence base for help-seeking refugees and asylum seekers is sparse and limited mainly to trauma-specific treatments [13–16], where in their recent review, Koesters, Barbui, and Purgato surmise: “Except for trauma-related conditions, there is almost no evidence on the efficacy of psychosocial interventions in this population” [12]. Trauma-focused therapies have demonstrated efficacy in reducing symptoms of PTSD, depression, and anxiety, but critically there are a limited number of studies considering other aspects such as daily functioning or quality of life; furthermore, it is not yet clear how to best manage distress by PMLDs [11, 15].

Although high-income countries, such as Austria, have one of the highest densities of mental health professionals, the proportion of trauma specialists is rather low and traumatized people often do not receive timely and appropriate treatment [17, 18]. Specialized treatment facilities are overwhelmed by the large numbers of treatment seekers, resulting in long waiting lists of up to more than a year [19, 20]. Adult survivors of traumatic events show specific barriers to treatment that are related to their trauma symptoms [21]. Additionally, refugees from non-Western countries may have a different conceptualization of mental illness and its treatment [22], where Afghan refugees have a relatively low mental health literacy [23]. Indeed, culturally adapted and evidence-based treatments within stepped or collaborative care systems are needed [24]. Barriers toward treatment acceptance might be further reduced by low-intensity treatments that do not focus on traumatic experiences, facilitating motivation for more intense trauma focused therapy, if needed [25]. On balance, low-intensity treatments in general seem to be effective in reducing mental health problems [﻿27﻿, 28]. Although low-intensity treatments are sometimes delivered by trained lay health workers [﻿26﻿], their effectiveness might be further strengthened if delivered by mental health professionals. Whereas psychotherapy is longer in duration, low-intensity interventions could be provided to a larger number of help-seeking refugees in shorter time and thus could constitute an important first step toward recovery.

Transdiagnostic approaches may be appropriate first-line treatments for help-seeking traumatized individuals; however, there is a lack of evidence for these treatments in refugee populations [﻿28﻿], where factors moderating treatment effectiveness should also be identified [15]. Problem Management Plus (PM+) is a recently developed, low-intensity, transdiagnostic treatment manual for individual settings and was developed by the World Health Organization (WHO) [﻿29﻿, ﻿30﻿]. PM+ was developed to help adults impaired by distress in communities who are exposed to adversity, regardless of whether exposure to adversity has caused their problems [﻿27﻿]. Here, transdiagnostic approaches are based on research suggesting that there are significant commonalities across emotional disorders (e.g., [55]). Furthermore, research has shown that a substantial number of people with mental disorders do not have a single disorder but rather have more than one comorbid conditions [56, 57]. Furthermore, PM+ is a suitable protocol for refugee populations because it was developed as a culturally adaptable and broadly applicable treatment. Transdiagnostic manuals address symptoms of common mental disorders without tailoring the treatment protocol to specific disorders [31]. PM+ was evaluated in studies in Kenya and Pakistan; both research teams were part of the larger PM+ research group. Research in Kenya [26, 32] showed that PM+ was more effective in reducing mental health problems than enhanced usual care (EUC). The main outcome was a change in psychological distress (assessed with the General Health Questionnaire 12, or GHQ-12) from baseline to 3 months post-treatment. Women who received PM+ reported significantly less psychological distress, with a moderate effect relative to EUC. The secondary outcomes (PTSD symptoms and functional impairment) also showed significant reductions but these effects were small relative to EUC. Research in Pakistan [33, 34] investigated PM+ in adult primary care attendees in a conflict-affected area. The treatment arm (PM+) showed significant reduction in the primary outcome, anxiety and depression symptoms (assessed with the Hospital Anxiety and Depression Scale, or HADS), with a moderate to large effect relative to EUC. The secondary outcomes (PTSD symptoms, functional impairment, and symptoms of depressive disorder) also showed significant reductions; these effects were moderate relative to EUC. Here, Khan and colleagues [35] report in their qualitative evaluation that PM+ was considered useful by participants, their families, and lay helpers. Other studies showed less clear results, where the treatment did not significantly reduce psychological distress symptoms in two studies [36, 37], although both of these studies were planned and conducted as pilot trials. However, the trends were in favor of a symptom reduction in the treatment arm in all measures compared with the control group in both studies.

Critically, this is the first study to implement a short-term protocol that will address the needs of adult refugees above and beyond trauma-related symptoms. Furthermore, as part of the present study, we will expand the PM+ manual by including interventions specifically addressing PMLDs.

### Objectives

The aims of this study are to evaluate the efficacy of a short-term transdiagnostic treatment protocol (adapted PM+) to address mental health problems and post-migration living difficulties for treatment-seeking Afghan asylum seekers and refugees who are on a waiting list for professional mental health treatment. This intervention aims to reduce typical symptoms of common mental disorders and associated distress via PMLDs.

We hypothesize that participants in the intervention group will show a significant reduction in general mental distress. Additional aims are to investigate the effectiveness of the intervention in (a) reducing symptoms of PTSD and complex PTSD, (b) alleviating the burden associated with PMLDs, (c) improving refugee’s quality of life, and (d) investigating the participants’ subjective experience and tolerance of the intervention.

## Methods

### Trial design

This study is designed as a prospective, single-center, assessor-masked, individually randomized, two-group superiority trial. It will compare a six-session transdiagnostic, low-intensity manualized psychological treatment with treatment as usual (TAU). The treatment group will receive TAU and adapted PM+; the control group will receive TAU only. Both groups will be recruited from a professional mental health treatment wait list. The trial design is depicted in the Consolidated Standards of Reporting Trials (CONSORT) flowchart in Fig. 1 [38], the Standard Protocol Items: Recommendations for Interventional Trials (SPIRIT) participant timeline is shown in Table 1, and the SPIRIT checklist [39] is provided as Additional file 1.

**Fig. 1 Fig1:**
[figure not shown]
Consolidated Standards of Reporting Trials (CONSORT) flowchart of the study design

**Table 1 Tab1:**
[figure not shown]
Participant timeline for the Standard Protocol Items: Recommendation for Interventional Trials (SPIRIT)

### Study setting

The trial setting is the Outpatient Unit for Research, Teaching, and Practice, Faculty of Psychology, University of Vienna. All assessments, in-depth interviews, and treatment sessions will take place in a separate room, and only the participant, the psychologist, and the interpreter will be present in the room.

### Participants

The study will include help-seeking, Dari-speaking adult Afghan asylum seekers or refugees who fulfil the following inclusion criteria: (a) being on a wait list for professional mental health treatment in a specialized facility and (b) positive screening on a screening questionnaire for common mental disorders in refugees (a score of 12 or higher on the RHS-15 or a score of 5 or higher on the distress scale of the RHS-15).

Exclusion criteria are (a) presenting with a current condition requiring other treatment (acute suicidality, severe mental disorder such as psychotic disorders or substance dependence), (b) severe cognitive impairment (e.g., moderate to severe intellectual disability or dementia), based on definitions in the Mental Health Gap Action Programme (mhGAP) Intervention Guide [40], or (c) current trauma-focused treatment.

### Intervention

This study uses an adapted version of PM+ in the intervention arm. PM+ [29] is a transdiagnostic, low-intensity psychological treatment for common mental disorders (e.g., depression, anxiety, and stress). It was developed by the WHO as part of its mhGAP [41]. PM+ was developed to help adults impaired by distress in communities that are exposed to adversity, regardless of whether exposure to adversity has caused their problems [29]. The original PM+ manual comprises four core therapeutic strategies that were chosen on the basis of a strong evidence base and following review by international experts [30]. These four core strategies are “Managing Stress”, “Managing Problems”, “Get Going, Keep Doing”, and “Strengthening Social Support”. Our modification of the treatment protocol includes an additional sixth session, focusing on either anger regulation or self-efficacy. This extra session is based on the specific needs of treatment-seeking refugees. It was developed by the research team in the initial phase of the study and includes the results from our preliminary study interviewing experts in the field. Participants will decide during the course of the treatment whether they prefer a session on anger regulation or on self-efficacy, depending on their subjective needs. According to Austrian law, only medical doctors and mental health specialists (clinical psychologists, psychotherapists) have official approval to treat mental disorders. Consequently, the treatment will be implemented by clinical psychologists who have a legal treatment allowance in Austria. Participants have six weekly face-to-face appointments (five from the original protocol and one developed as part of this study); the duration of these sessions is 90 min. The sessions will be facilitated by interpreters. The psychologists will be specifically trained by PM+ master trainers. Regular supervision will guarantee therapist adherence to the protocol. Treatment fidelity will be scored by using the PM+ Helper’s Self-rating Fidelity Checklist. The checklist records delivery of the intervention, psychosocial communication, and safety management skills. The treatment group will receive TAU and adapted PM+.

### Control condition

This study uses a control arm to control for possible spontaneous remission and other uncontrolled factors. The control arm will be assessed at the same time points as the treatment arm but will not receive any treatment by the research team. During the period between pre-assessment and follow-up assessment, participants from this arm will receive TAU in their daily living conditions. We expect that the control arm in this study will receive treatments that are commonly implemented in the Austrian medical settings; this includes any contact with medical and mental health professionals or pharmacological therapy. Receiving psychopharmacological or psychological treatment is considered TAU and does not preclude a person from the control arm.

### Outcome measures

#### Primary outcome

The primary outcome is the general health assessed with the General Health Quenstionnaire 28 (GHQ-28) [42], which is a 28-item self-report questionnaire assessing somatic symptoms, anxiety and insomnia, social dysfunction, and severe depression. The GHQ-28 is widely used in research across different cultural settings and has good psychometric properties [43]. The GHQ-28 will be assessed by investigators blind to treatment allocation at baseline, 7-week follow-up, and 6-month follow-up. We will use the German and Dari versions of the questionnaire.

#### Secondary outcomes

We will also use several secondary endpoints: an adapted Version of the Post-Migration Living Difficulties Checklist (PMLDC) [43], the International Trauma Questionnaire (ITQ) [45], the WHO Quality of Life Questionnaire (WHOQOL-BREF) [44], the Psychological Outcome Profile (PSYCHLOPS) [46], and the Immigrant Integration Index (IPL-12).

The PMLDC is a self-evaluated checklist used to assess the frequency of recent adverse life experiences typical of migration [5]. The checklist was adapted to the study population. The final version includes 26 items measured on a 5-point Likert scale. In addition, the associated degree of distress is assessed on a 10-pont Likert scale. The ITQ is an instrument designed to assess ICD-11 (International Classification of Diseases, 11th ed.) PTSD and complex PTSD. The ITQ includes six items for PTSD, six items for complex PTSD, and two times three items for functional impairment by symptoms of PTSD and complex PTSD [48]. The ITQ has shown good psychometric properties in initial validations [49]. The WHOQOL-BREF is a cross-culturally comparable instrument to assess quality of life. It consists of 26 items measured on a 5-point Likert scale. It is divided into four domains: physical health, psychological health, social relationships, and environment. The PSYCHLOPS promotes a patient-centered definition of therapy outcome and contains questions on problems, function, and well-being. Participants are asked to describe their main problem or problems and how they affect them (function) with five questions. The short version of the IPL-12 [44] is a pragmatic and multidimensional measure of immigrant integration. It consists of 12 items and captures six dimensions of integration: psychological, social, economic, political, linguistic, and navigational. We are using the available Dari and German versions and translating the remaining Questionnaires.

### Additional measures

Traumatic experiences will be assessed with an adapted version of the Trauma Checklist of the Harvard Trauma Questionnaire [51] (Dari and German version). The Service Use Questionnaire (Client Service Receipt Inventory) is used to collect data about the health-care contacts.

### Sample size

Studies using the original PM+ manual so far have found small to large effects compared with TAU at 6 months post-treatment. Assuming an α error probability of 0.05 and a power (1-β error probability) of 0.80, we need a total sample size of 90 persons (45 persons per group) when testing for a medium effect (*f* = 0.3). We chose the more conservative approach and assumed only small effects of the treatment and thus aim to include 90 persons in the analysis. We expect a dropout rate of 25%. Taking this into account, we aim to include a total of 120 participants who will be randomly assigned to either the intervention arm (*n* = 60) or the TAU arm (*n* = 60). A subgroup of the intervention arm (*n* = 20) will be invited for in-depth interviews.

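### The sample-size paragraph attributes the same 90 analysed participants to a medium effect (f = 0.3) and to a conservative assumption of small effects; 90 matches f = 0.3, and 80% power for a small effect is not shown.

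*Protocol article*

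**What the plan says.** The Sample size section of the protocol article sets out its inputs as follows.

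- Error rates: "Assuming an α error probability of 0.05" and "a power (1-β error probability) of 0.80".
- Required number: "we need a total sample size of 90 persons (45 persons per group) when testing for a medium effect", with the effect given as f = 0.3.
- Next sentence: "We chose the more conservative approach and assumed only small effects of the treatment and thus aim to include 90 persons in the analysis".
- Dropout of 25% is then allowed for, giving 120 randomised, 60 per arm.

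The paragraph opens by saying that earlier studies of the unadapted manual found "small to large effects compared with TAU at 6 months post-treatment". No numerical value is given for a small effect, and there is no second calculation. The Statistical analyses section plans a hierarchical linear model with time, treatment and their interaction. The primary outcome section lists three assessments: baseline, 7 weeks and 6 months. The sample-size paragraph gives no number of measurements and no within-person correlation.

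**The concern.** The same number is given two incompatible bases. If 90 is what a medium effect requires, moving to a smaller effect at the same alpha and power has to increase it. Here the number stays put, yet the text presents it as the result of a more cautious assumption.

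This paragraph is the only justification given for the size of the trial. A reader who relies on its last step would take the trial to be adequately powered for small effects. Small effects are realistic on the protocol's own account: the Background reports small effects on the secondary outcomes in the Kenya trial and two pilot trials without a significant reduction in distress. If the result is not significant, how far it speaks against a small benefit depends on the effect the trial was actually sized for.

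**Working it through.** **Inputs.** From the protocol: alpha 0.05, power 0.80, f = 0.3, 90 analysed in two equal groups, 25% dropout. Assumed here: a two-sided test (the protocol does not state sidedness), small effects taken over a range of f with the conventional f = 0.10 at the lower end, and correlations of 0.3 to 0.7 where a model needs one.

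**Step 1: reproduce the plan's figure.** For a two-group F test the noncentrality is λ = N × f², with 1 and N − 2 degrees of freedom. For two equal groups d = 2f.

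- f = 0.3 gives d = 0.6 SD.
- N = 90: λ = 90 × 0.09 = 8.1, power 80.4%.
- N = 88: power 79.5%.

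So 90 is exactly the smallest even total for f = 0.3. Dropout: 90 / (1 − 0.25) = 120, which also agrees. The smallest f with 80% power at N = 90 is 0.299.

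**Step 2: same test, smaller effects.**

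| f | d = 2f | Power with 90 analysed | Total analysed for 80% power |
|---|---|---|---|
| 0.30 | 0.6 | 80% | 90 |
| 0.25 | 0.5 | 65% | 128 |
| 0.20 | 0.4 | 47% | 200 |
| 0.15 | 0.3 | 29% | 352 |
| 0.10 | 0.2 | 16% | 788 |

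If all 120 were analysed, power at f = 0.10 would be 19%.

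**Step 3: other tests at f = 0.10 with 90 analysed.**

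- One-sided test: 24%.
- Baseline-adjusted comparison, SD multiplied by √(1 − r²), r = 0.3 to 0.7: 17% to 26%.
- Repeated-measures between-group test, λ = N m f² / (1 + (m − 1)ρ), m = 2 or 3 measurements, ρ = 0.3 to 0.7: about 18% to 25%.
- Group-by-time interaction, λ = N m f² / (1 − ρ), same m and ρ: 35% to 76%.

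None reaches 80% at f = 0.10.

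**Step 4: can a smaller f also yield 90?** Yes, on the interaction scale. With f = 0.15, m = 2 and ρ = 0.5, λ = 90 × 2 × 0.0225 / 0.5 = 8.1, the same as in Step 1, so N is again 90. The two values of f are not on the same scale. With two groups and two times, if one cell differs from the other three by δ SD, the interaction component of each cell is ±δ/4, so f = δ/4. There f = 0.15 means δ = 4 × 0.15 = 0.6 SD difference in change, and f = 0.10 means 0.4 SD.

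**The case against.** The strongest defence is that the planned analysis is longitudinal, so a single-time-point calculation may understate power, and small has no stated value. That stands in part, and it rules out several stronger readings that a reader might infer.

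- *That power for a small effect simply is 16%.* That figure needs f = 0.10 and an unadjusted comparison at one time point. It is the low end of a range that depends on the model.
- *That no small effect could produce 90.* Step 4 shows one that does. At f = 0.15 on the interaction scale, several of the correlations tried give more than 80% power. This does not rescue the paragraph, which states f = 0.3 and gives no number of measurements or correlation.
- *That the trial can detect only 0.6 SD.* With baseline adjustment the detectable difference is about 0.597 × √(1 − r²), that is 0.57, 0.52 or 0.43 SD for r = 0.3, 0.5 or 0.7. A fixed rule for reading a null result at 0.6 SD would not match the planned model.
- *That the protocol expressly claims 80% power for small effects.* The 0.80 is attached to f = 0.3. The next sentence names no power; it only implies adequacy.
- *That the evidence sentence is wrong and should read 3 months.* The Background uses "from baseline to 3 months post-treatment" only for the main outcome of the Kenya trial and gives no time point for the other studies. Its reported effects, small to moderate-to-large, fit the stated range. What remains is a difference of comparator: enhanced usual care for the Kenya and Pakistan trials in the Background, usual treatment in the Sample size section.

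It is also fair to say that f, alpha, power, 90 and 120 agree with one another. The fault is a contradiction in the text, not an arithmetic slip.

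**Conclusion.** The point holds. The paragraph gives one number two bases that exclude each other, and nothing else in the protocol resolves it. The stated f = 0.3 reproduces 90 exactly in a two-group comparison, so the small-effect basis is a property that the design is not shown to have.

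Size: under an unadjusted two-sided comparison at one time point, power falls from 80% at f = 0.3 to between 65% and 16% for f from 0.25 to 0.10. At f = 0.10, adjustment or a repeated-measures test could bring it to roughly 17% to 76%. The upper part of that range comes from the interaction test, where f is on a different scale, and rests on correlations that the protocol does not give.

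**What to change.** Delete the sentence about a more conservative approach and small effects. In its place, state that 90 analysed participants give 80% power for f = 0.3, equal to 0.6 SD in an unadjusted two-group comparison. Name the model that the calculation refers to and any correlation assumed, and give the lower power for smaller effects under that same model. If the team does intend to power for a small effect, it must state its value and recompute the number.

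Separately, check the opening sentence on effects against usual treatment at 6 months against its sources, and reconcile the comparator with the Background. It should not simply be changed to 3 months.

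The first route costs only protocol wording. Enrolment stays at 120, and the price is a less favourable statement of power. Recomputing for a small effect would be a different matter: in the unadjusted comparison, f = 0.20 needs 200 analysed, or 200 / 0.75 = 267 randomised.
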